## Abstract

**Background:**

Germline *BRCA1* and *BRCA2* mutation testing offered shortly after a breast cancer diagnosis to inform women’s treatment choices - treatment-focused genetic testing ‘TFGT’ - has entered clinical practice in specialist centers and is likely to be soon commonplace in acute breast cancer management, especially for younger women. Yet the optimal way to deliver information about TFGT to younger women newly diagnosed with breast cancer is not known, particularly for those who were not suspected of having a hereditary breast cancer syndrome prior to their cancer diagnosis. Also, little is known about the behavioral and psychosocial impact or cost effectiveness of educating patients about TFGT. This trial aims to examine the impact and efficiency of two models of educating younger women newly diagnosed with breast cancer about genetic testing in order to provide evidence for a safe and effective future clinical pathway for this service.

**Design/methods:**

In this non-inferiority randomized controlled trial, 140 women newly diagnosed with breast cancer (aged less than 50 years) are being recruited from nine cancer centers in Australia. Eligible women with either a significant family history of breast and/or ovarian cancer or with other high risk features suggestive of a mutation detection rate of > 10% are invited by their surgeon prior to mastectomy or radiotherapy. After completing the first questionnaire, participants are randomized to receive either: (a) an educational pamphlet about genetic testing (intervention) or (b) a genetic counseling appointment at a family cancer center (standard care). Each participant is offered genetic testing for germline *BRCA* mutations. Decision-related and psychosocial outcomes are assessed over 12 months and include decisional conflict (primary outcome);uptake of bilateral mastectomy and/or risk-reducing salpingo-oophorectomy; cancer-specific- and general distress; family involvement in decision making; and decision regret. A process-oriented retrospective online survey will examine health professionals’ attitudes toward TFGT; a health economic analysis will determine the cost effectiveness of the intervention.

**Discussion:**

This trial will provide crucial information about the impact, efficiency and cost effectiveness of an educational pamphlet designed to inform younger women newly diagnosed with breast cancer about genetic testing. Issues regarding implementation of the trial are discussed.

**Trial registration:**

The study is registered with the Australian and New Zealand Clinical Trials Group (Registration no: ACTRN12610000502033)

## Background

The clinical role of *BRCA1* and *BRCA2* mutation testing for younger women with breast cancer is in rapid transition because of advances in gene sequencing technologies and accumulating evidence for the contribution of *BRCA* mutation status to acute management of early breast cancer. Women diagnosed with breast cancer are offered genetic counseling and testing for germline mutations in *BRCA1* and *BRCA2* if they have a strong family history of the disease and/or they meet other criteria which point to a mutation detection rate that exceeds a predefined threshold for her local service. Genetic risk assessment has usually been offered on completion of surgery and adjuvant therapy for a new breast cancer, and routine genetic test results in Australia has to date taken between one and six months from blood draw. In contrast, genetic counseling and testing offered around the time of breast cancer diagnosis aims to provide the patient with genetic information that will assist in the choice of breast cancer treatment, primarily the choice between breast-conserving therapy (BCT) and mastectomy. The secondary effects of directing risk-reducing ovarian surgery and informing family members of their own cancer risks are not time dependent but useful outcomes of a genetic test at any time.

Women newly diagnosed with breast cancer with a *BRCA* mutation must choose whether to undergo BCT, unilateral mastectomy, or prophylactic bilateral mastectomies to prevent future breast cancers [1]. The incidence of another tumor developing in the treated breast increases in *BRCA* mutation carriers with longer follow-up [1] and it also varies with the type of local therapy [2]. Pierce et al. found that there was a significantly increased risk of local tumor recurrence in *BRCA1* and *BRCA2* mutation carriers treated with BCT compared to carriers treated with mastectomy at 10 years (10.5% versus 3.5%) and at 20 years (30.2% versus 5.5%) [2]. Compared with noncarriers, *BRCA1* and *BRCA2* mutation carriers have a substantially increased lifetime risk of contralateral breast cancer that is age dependent and can be up to 68%, if the age of the first cancer is <40 [3,4]. While there is no evidence that prophylactic mastectomy improves breast cancer survival for *BRCA* mutation carriers [5], the risk of and potential emotional impact of a subsequent breast cancer and the need for further treatment are important issues to consider [1]. Contralateral prophylactic mastectomy can decrease the risk of subsequent breast cancer by up to 95% [6-8]. The *BRCA* mutations also confer a 13-46% lifetime risk of ovarian cancer [9]. The secondary breast cancer prevention role of premenopausal risk-reducing bilateral salpingo-oophorectomy (RRSO) is less well established. Although there is an important breast cancer risk reduction of between 39% (*BRCA1*) and 72% (*BRCA2*) [10] among mutation carriers who have RRSO before the age of 50 years, Domchek et al. 2010 did not find a similar reduction in women who had had prior breast cancer [8]. *BRCA1* and *BRCA2* mutation testing can now be made available rapidly, within 5 working days if required. Soon, further advances in sequencing will substantially reduce the cost of genetic analysis [11] and will open the opportunity for genetic testing to even more women who might benefit from this information. This means that a woman’s *BRCA* mutation status can feasibly be used now to inform her surgical decisions regarding BCT or mastectomy (unilateral or bilateral). In the future, timely *BRCA* mutation testing will extend to selection of specific adjuvant systemic chemotherapy once the optimal systemic therapy for *BRCA* mutation carriers is established, including the role of poly (ADP-ribose) polymerase (PARP) inhibitors [12,13] and platinum-based chemotherapy. Hereafter, genetic counseling and testing offered shortly after a women’s diagnosis of breast cancer will be referred to as ‘treatment-focused genetic testing’ (TFGT). The potential for ever increasing scope for the use of TFGT in acute breast cancer management in the very near future means that new models for genetic counseling will be needed in order to manage the increased demand for and delivery of genetic information. In particular, there is a pressing need to develop cost effective clinical pathways which utilize the multidisciplinary cancer and genetics team, in order to offer TFGT in a streamlined way which is acceptable to patients and health care providers.

A concern shared by both patients and health professionals is that TFGT may create undue psychological burden among women diagnosed with breast cancer at a very vulnerable time in their life [14]. There is limited empirical data available on the psychosocial implications of TFGT. Two studies have described the behavioral and psychological impact of TFGT in the US [15-17] and The Netherlands [18]. In the US study, 194 patients newly diagnosed with breast cancer were offered genetic testing before definitive treatment and the impact on surgical decision-making was evaluated. Definitive treatment was defined as mastectomy (unilateral or bilateral) or BCT, including commencement of radiation treatment [15]. Forty-eight percent of women who were found to carry a *BRCA1* or *BRCA2* mutation opted for bilateral mastectomy (BM), compared to 4% of women who declined genetic testing. Compared to women who chose BCT or unilateral mastectomy, those who chose BM did not report diminished quality of life or increased distress [17]. The Dutch prospective study assessed the psychological impact of TFGT in women diagnosed with breast cancer who were about to commence adjuvant radiotherapy. Patients’ distress levels did not increase after genetic counseling and testing [18]. Another randomized controlled trial is currently in progress in The Netherlands, which is assessing the impact of rapid genetic testing and counseling on women newly diagnosed with breast cancer on surgical decision making and psychosocial outcomes [19].

A limitation of these studies is that they have selected or are selecting women based primarily on a significant family history of breast and/or ovarian cancer [16,18] or have retrospectively selected women based upon their *BRCA* mutation status [14]. In addition, these previous studies have not included a health economic analysis assessing the cost effectiveness of delivering TFGT to women diagnosed with breast cancer. The concept of a strong family history as the optimum criterion for selection for genetic testing is being challenged with evidence for several personal and disease characteristics that are suggestive of *BRCA* mutations. For example, between 30-50% of women with a *BRCA1/2* mutation have no significant or known family history of breast or ovarian cancer [20,21] and up to 8% of women with Ashkenazi Jewish ancestry and breast cancer diagnosed under 50 years have no relevant family history [22]. Up to 27% of women under the age of 50 and 36% of women diagnosed at or under age 40, unselected for family history with triple negative breast cancer are *BRCA1* mutation carriers [23]. Of over 12,000 new breast cancer diagnoses in Australia annually, 24% are in women under 50 [24]. In relation to genetic testing, the predictive value of having a *BRCA* mutation in these younger age-of-onset cases increases especially when combined with triple negative disease [25]. Yet little is known about the acceptability of TFGT among younger women without a relevant cancer family history but with disease, tumor or ethnic features suggestive of a high risk of actually having a *BRCA* mutation. Meiser and colleagues conducted in-depth semi-structured interviews with 26 younger women (aged 50 years or less) diagnosed with breast cancer (14 had undergone TFGT and 12 had not), which explored their actual and hypothetical attitudes toward, and experiences (if any) of TFGT [26], and their information preferences regarding TFGT [27]. Women with and without a relevant family history of breast and/or ovarian cancer were included. All of the participants viewed TFGT as highly acceptable and wanted to receive information about it early, either at diagnosis or shortly thereafter, to inform their treatment options and to assist family members. Women preferred to receive the offer of TFGT verbally in a face-to-face consultation with a health professional. However, they also highlighted the importance of provision of supportive brief written information about TFGT that they could take away and consider at home [27].

In this paper, we report the design of a study that compares two different models of delivering information about TFGT to younger women newly diagnosed with breast cancer. We also report several key issues encountered in the implementation of the study, which will have important implications for the integration of TFGT into acute breast cancer management in the near future.

### Study objectives and hypotheses

The aim of this study is to compare the behavioral and psychosocial impact, efficiency and safety of offering information about TFGT to younger women newly diagnosed with breast cancer (a) using a brief educational pamphlet about TFGT (educational materials, ‘EM’ intervention) or (b) using pre-test genetic counseling at a family cancer service (standard care, ‘SC’ control). The efficiency of offering information about TFGT will be operationalised in a health economic analysis and through an assessment of health professionals’ views on the effectiveness of the TFGT process. The safety of the intervention will be determined by assessing its impact on psychological distress. This is a non-inferiority trial, in which our primary hypothesis is that patient decisional conflict regarding TFGT will be no worse in the intervention compared to that of the control group. A summary of the research questions that are addressed in the study are presented in Figure 1.

**Figure 1 F1:**
[figure not shown]
Research questions addressed in the study.

Our secondary hypotheses are: (i) that other decision-related and psychological outcomes (including decision regret regarding TFGT and surgery; anxiety; depression; cancer-specific distress; test-related experiences and distress; knowledge of TFGT; and uptake of genetic testing) will not be inferior in the intervention group compared to the control group, and (ii) that women who opt for TFGT will have a higher uptake of BM compared to data from the Royal Australasian College of Surgeons National Breast Cancer Audit on over 12,000 women with early breast cancer diagnosed annually [28].

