## Methods

### Participants

A woman is eligible to participate if she is aged less than 50 years at diagnosis of invasive breast cancer or ductal carcinoma *in situ* and has not had a mastectomy for her current cancer or radiotherapy at the time of invitation. The eligibility and exclusion criteria are presented in detail in Figure 3. The patient must have (A) either a strong family history of breast and/or ovarian cancer, specifically (i) three or more affected relatives including the patient on one side of the family or (ii) two or more affected relatives including the patient on one side of the family and a high-risk feature [31], or (B) in the absence of a relevant family history, the woman must have at least one of the following high risk features: bilateral breast cancer; and/or Ashkenazi Jewish heritage, and/or a triple negative tumor. 

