### Statistical power

It is estimated that less than 10% of breast cancer patients of all ages will be eligible for the study.

A total sample size of 128 has 80% power to test the non-inferiority of the intervention on the primary outcome, the Decisional Conflict Scale (DCS). For the DCS, a non-inferiority margin will be -10 units, that is, the intervention group will be considered no worse than the standard care group if the 95% CI of the mean difference in DCS between the two groups lies wholly above -10 units. The DCS has 10 items, with the following response options: ‘Yes’, ‘Unsure’ and ‘No’ to items such as: ‘Do you know which options are available to you?’ The DCS total score ranges from 0 to 100 and thus a non-inferiority margin of -10 units on the DCS corresponds to only one of the 10 items having been endorsed as ‘No’ instead of ‘Yes’. The power calculation is based on a 5% significance level (2-sided), a true mean difference of zero units and a conservative SD of 20 units.

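### Hypothesis (ii) compares bilateral mastectomy uptake in selected high-risk women under 50 with an audit for which no restriction is stated, so it could be confirmed even if TFGT had no effect on surgical choice

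*Protocol article*

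**What the plan says.** Under Study objectives and hypotheses, hypothesis (ii) fixes the group, outcome, direction and comparator: "women who opt for TFGT will have a higher uptake of BM compared to data from the Royal Australasian College of Surgeons", the source being the "National Breast Cancer Audit on over 12,000 women with early breast cancer diagnosed annually". No restriction of the audit data by age, risk or laterality is given.

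The trial population is narrower. Under Methods, Participants, a woman must be "aged less than 50 years at diagnosis of invasive breast cancer or ductal carcinoma" in situ. She must also have a strong family history or, failing that, at least one of "bilateral breast cancer; and/or Ashkenazi Jewish heritage, and/or a triple negative tumor". Women who have already had a mastectomy for the current cancer are not eligible.

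Two further figures show the distance between the populations. The Background says "Of over 12,000 new breast cancer diagnoses in Australia annually, 24% are in women under 50", and Statistical power expects that "less than 10% of breast cancer patients of all ages will be eligible for the study".

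Uptake of BM is a listed secondary outcome under Design. Statistical analysis describes comparisons between the randomised arms and over time, and does not mention the audit.

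**The concern.** Hypothesis (ii) is a comparison with an external group, and the two groups differ in more than TFGT.

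- **Age.** All participants are under 50. If the audit has the national age mix, about 76% of its women are older than any participant.
- **Risk.** Participants are chosen for family history or high-risk features. The audit as described is not.
- **Laterality.** Bilateral cancer is itself a way into the trial. When such a woman has BM, cancer was already present in both breasts, so the operation is weak evidence that TFGT altered a choice. Hypothesis (ii) still counts it as uptake.

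The trial has no internal comparison that would correct this. Both arms are offered TFGT, so randomisation does not contrast TFGT with no TFGT. The Discussion reports that all 110 women enrolled by June 2012 chose testing, so at that point there was no untested group either. The audit is the only stated reference. What is at stake is a conclusion about TFGT and surgical choice, in a trial meant to inform routine care, that the comparison cannot support.

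**Working it through.** **The plan's own figure.** The only power figure is for the primary outcome: margin 10, SD 20, 5% two-sided, 80% power. Per arm, 2 × (1.96 + 0.8416)² × (20/10)² = 62.8, so 63 per arm and 126 in total. With the t distribution, 64 per arm gives 80.1% power, which reproduces the stated 128. No figure is given for hypothesis (ii).

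**Inputs for hypothesis (ii).** From the article: 140 women randomised, and 24% of national diagnoses under 50. Assumed, because the article does not give them: the audit BM rate p0, the share b of trial women with bilateral cancer, and the proportion q of those women who have BM. The test is also assumed: a one-sample exact binomial test of the trial rate against a fixed p0 at one-sided 2.5%, with all 140 women opting for TFGT.

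**Step 1: bilateral cancer alone, TFGT effect set to zero.** The trial rate is p1 = b·q + (1 − b)·p0. For example, p0 = 3%, b = 5% and q = 80% give 0.05 × 0.80 + 0.95 × 0.03 = 6.85%. The hypothesis is confirmed when the BM count reaches the smallest r with P(X ≥ r | 140, p0) ≤ 0.025. The false-confirmation probability is P(X ≥ r | 140, p1). Each cell below gives q = 50% / 80% / 100%.

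| Audit rate p0 | r | Size if p1 = p0 | b = 2% | b = 5% | b = 10% |
|---|---|---|---|---|---|
| 3% | 10 | 1.0% | 5 / 11 / 16% | 22 / 49 / 67% | 64 / 94 / 99% |
| 5% | 13 | 2.4% | 7 / 12 / 17% | 22 / 45 / 62% | 58 / 90 / 98% |
| 8% | 19 | 1.6% | 4 / 7 / 9% | 11 / 27 / 40% | 35 / 74 / 90% |

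The range is about 4% (p0 = 8%, b = 2%, q = 50%) to 99% (p0 = 3%, b = 10%, q = 100%). The third column shows what a comparator with the same underlying rate would give: at most 2.5%.

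**Step 2: age alone.** Suppose the audit has the national age mix, an overall BM rate of 4%, and an under-50 rate k times the older rate. The under-50 rate is then k × 4% / (0.76 + 0.24k), and r = 12.

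- k = 1: 4.0%, false confirmation 1%
- k = 2: 8%/1.24 = 6.5%, false confirmation 19%
- k = 3: 12%/1.48 = 8.1%, false confirmation 46%
- k = 4: 16%/1.72 = 9.3%, false confirmation 66%

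The values of k are assumptions; the article does not say how BM varies with age.

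**The case against.** Several points on the other side have force.

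- **Is confirmation assured?** A reader might infer that hypothesis (ii) is bound to be confirmed whatever TFGT does. The documents do not support that. Every rate needed is missing, and in many cells of the table non-confirmation is the likelier result. This objection stands.
- **Does the article claim causation?** Read literally, hypothesis (ii) predicts only a higher uptake. That also stands. But the group is defined by opting for TFGT, and the Background presents TFGT as help in choosing surgery, so an effect reading is invited.
- **Is there evidence of a high baseline?** The article does not show that age or family history raises BM without testing. The one nearby figure, from the US study in the Background, is 4% among women who declined testing. Decliners are self-selected, so this neither proves a low baseline nor makes the audit comparable.
- **Does selection also work the other way?** Excluding women with a prior mastectomy could lower the trial's BM rate. An unrestricted audit would also contain some bilateral cases, so what matters is the trial's excess share. Both points stand. Their size is unknown, and they may shrink the bias.
- **Is this detail for the full protocol or SAP?** An age-restricted extract may be specified there, and the article does not rule one out. But the hypothesis as printed names its comparator without restriction, and only a change to the comparator or its label removes the mismatch.

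**Conclusion.** The concern holds in a limited form. As written, hypothesis (ii) sets a young, high-risk group that can include women with bilateral cancer against an audit with no stated restriction. It could be confirmed with no effect of TFGT on surgical choice. Against a nominal 2.5%, the chance is about 4% to 99% from bilateral cancer alone, over assumed audit rates of 3-8%, bilateral shares of 2-10% and 50-100% of bilateral cases having BM. The prior-mastectomy exclusion, not modelled here, could bring it down. The width of that range is itself a result: with the information in the article, a higher BM rate could not be interpreted. It would be wrong to conclude that confirmation is certain, or that the article asserts a causal effect. The randomised comparison of decisional conflict and its sample size of 128 are not affected.

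**What to change.** Amend hypothesis (ii) and the matching analysis text as follows.

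1. Restrict the audit extract to women under 50 at diagnosis in the same calendar years as recruitment, age-standardised to the trial where the audit allows.
2. Exclude women with bilateral cancer at diagnosis from numerator and denominator on both sides, and report them separately. Laterality should be confirmed for every participant, including those who qualify through family history.
3. Label the comparison descriptive and state that it does not estimate an effect of TFGT, because family history and triple-negative status may remain unmatched. State also that the trial excludes women with a prior mastectomy.
4. BM by mutation status may be reported as supportive and non-randomised. It should not replace the audit comparison, since it asks what the test result does and not how uptake compares with usual practice. Carriers may also be few among 140.

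The cost is a more specific tabulation from an audit already to be used, some wording, and a few women lost from the BM denominator. Randomisation, sample size and the primary analysis do not change.

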### Design

This is a multicenter randomized controlled trial which is being conducted at nine hospital sites located in three states in Australia (New South Wales, Victoria and Queensland) in two stages. The study protocol adheres to CONSORT guidelines [29]. The study design is presented in Figure 2. In Stage I, 140 eligible patients are being randomized to receive either EM or SC. Randomization is in a 1:1 ratio and is achieved through a computerized random sequence, which is generated by an independent person. Each number in the sequence is printed and placed in an unmarked envelope such that allocation is concealed from the study coordinator until randomization occurs. It is not possible to blind participants to their allocation because they become aware of it once the genetics staff arrange patients’ genetic counseling appointments. The primary outcome measurement is level of decisional conflict regarding TFGT. The secondary behavioral and psychological outcome measures include: (i) uptake of TFGT; (ii) uptake of BM; (iii) cancer-specific distress; (iv) general anxiety and depression; (v) distress associated with decision to have genetic testing; (vi) level of decision regret regarding TFGT and surgical decisions, and (vii) family involvement in decision-making. Over the course of the study, four questionnaires will be administered: at baseline (prior to randomization); one week after receiving education about TFGT; 3 weeks after receipt of genetic testing result (or at the equivalent time point for those who do not have genetic testing or who choose not to receive their test result); and 12 months after study enrolment. 

